# Multivariable regression

To account for the clustering as well as to adjust for potential confounding, we will adjust the final results using a multivariable regression model. We will use generalizing estimating equations (GEE) 24 to estimate the log odds of the intervention on inappropriate treatment proportion compared to the control group. Use of GEE will allow us to adjust variance estimates (providing robust standard errors) to account for the clustering of cases within a cluster. The correlation matrix will be defined as compound symmetry. Odds ratios and 95% confidence intervals will be used to summarize the data.

# 6.2 Secondary end-point comparison

The secondary outcomes are:

1. To measure the proportion of children managed in each study arm who does not respond to treatment (treatment failures).
2. To measure the cost-effectiveness of having CHWs manage presumptive malaria using Coartem® with and without the use of RDTs.
3. To measure the proportion of acute febrile illnesses in children which are RDT-positive.

The analysis of the secondary outcomes 1 and 3 would be similar to the analysis of the primary outcomes. The analysis of secondary outcome 2 is described below.

# 6.3 Analysis of economic outcomes

###### Univariate and multivariable analyses

Analyses will be conducted at the provider level (encompassing both households and facilities). We will calculate the mean costs of diagnosis and treatment of malaria pneumonia for intervention and control groups, their standard deviations, medians, and ranges. Group differences in costs will be assessed using chi-square tests. Univariate analyses will also be conducted for likely predictors of costs, including household socio-demographic characteristics (i.e., education of mother, household size), distance from household to nearest health facility, and treatment history details (i.e., referral to RHC, time from diagnosis to RHC visit, follow-up on referral, hospitalization).

We will conduct multivariate regression to estimate the effect of various factors, including household socio-demographic characteristics and study arm, on the total cost by day 5-7 of treatment of malaria.

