#### 3.3.1 Secondary Objectives

- To measure the proportion of children managed in each study arm who do not respond to treatment (treatment failures).
- To measure the cost-effectiveness of having CHWs manage malaria using Coartem® with RDTs compared to without the use of RDTs.
- To measure the proportion of acute febrile illnesses in children which are RDT-positive
- To determine the burden of non-malaria febrile illness among a rural population of children reporting fever

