# 4.2 Study design

The study will be a cluster-randomized controlled trial. A study cluster will be defined as the catchment area of a community health post. CHWs work from a community health post with well defined catchment area and population within a health facility catchment area and are supervised by the staff of the health facility. The clusters (community health post catchment area) will be matched in pairs according to the health facility catchment area they belong to, the distance from the health facility and the population size. Randomization will then be done from among the matched clusters to select the intervention and the control arms. CHWs in both the intervention and control arms will receive training in the assessment and classification of children presenting with fever and/or cough/difficult breathing. The CHWs in the intervention arm will be supplied with RDTs, Coartem® and amoxicillin. The intervention CHWs will be trained to use RDTs in patients with reported fever and provide those with a positive result with Coartem while patients suspected of pneumonia (based on fast breathing) will be treated with amoxicillin as per the standard of care at health facilities and monitored. Those with negative RDT result will be treated with antipyretic and asked to return if they do not get better after 48 hours or condition deteriorates. In the control group, no RDT will be performed. The CHWs will be supplied with Coartem to treat malaria/febrile illness as per the IMCI guidelines and patients suspected of pneumonia will be referred to the health facility for treatment as per the current practice. The supply of the drugs and RDTs will come through the normal MOH sources. The study will utilize specialized field workers (data collectors and data supervisors) to visit CHWs to collect data on their consultations and follow-up children treated by CHWs. Consent will be sought from caregivers to allow us collect data by which to assess the effectiveness of the intervention. Caregivers in both the intervention and control arms are not obliged to receive care from the CHWs. They are free to go to any of the health facilities in the study area instead of a CHW. The study will collaborate with the MOH and the DHMTs to ensure that the health facilities in the study area have RDTs, Coartem and amoxicillin.

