#### 4.18 Economic Analyses

The overall goal of the economic evaluation is to determine the cost effectiveness and the difference in economic costs between the use of RDTs in the diagnosis and treatment of malaria (the intervention) and the presumptive treatment of fever with Coartem (the control). The economic analysis will also determine the incremental cost-effectiveness of the use of RDTs in the diagnosis and treatment of malaria so as to provide an additional measure by which to judge the usefulness of the ZIMMAPS intervention. The economic analyses will be based both on cross sectional data collected from health facilities and data collected longitudinally from the caretakers of ill children. The key indicators will be direct economic costs incurred in both the treatment and control areas. We will measure such costs at the household, health care provider, and medical facility levels related to diagnosis and treatment of malaria and pneumonia by CHWs, including referrals. Health outcome will be measured as treatment failure defined earlier.

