###### Estimate of incremental cost per health outcome

Several of our specific secondary objectives will involve calculating cost-effectiveness ratios (CERs). Each CER will be estimated by calculating the difference in costs divided by the differences in health outcome according to the following standard cost-effectiveness formula:

*CER = (CA – CB) / OA – OB),*

Where C refers to total cost, O refers to outcome, A refers to the intervention group, and B refers to the control group.

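### Section 6.3 tests cost differences with chi-square tests, builds the cost-effectiveness ratio on treatment failure so that its sign is reversed, and labels a whole-package ratio as an RDT effect

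*Protocol*

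**What the plan says.** Section 6.2 lists cost-effectiveness as the second of three secondary outcomes. It applies the primary-outcome methods to the other two and sends this one to section 6.3.

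- **Cost comparison (6.3).** "We will calculate the mean costs of diagnosis and treatment of malaria pneumonia for intervention and control groups, their standard deviations, medians, and ranges". The next sentence is "Group differences in costs will be assessed using chi-square tests". A regression of total cost on study arm and household factors follows, with malaria treatment cost by day 5-7 as its outcome. Neither step mentions clusters.
- **Ratio (6.3).** "Each CER will be estimated by calculating the difference in costs divided by the differences in health outcome". The symbols are then defined: "Where C refers to total cost, O refers to outcome, A refers to the intervention group, and B refers to the control group". The numerator is CA - CB and the denominator OA - OB.
- **Outcome in the ratio (4.18).** "Health outcome will be measured as treatment failure defined earlier". Section 3.5 defines failure as a composite. One component is the use of antibiotics or antimalarials additional to those the community health worker (CHW) gave.
- **What the ratio is meant to show (3.3.1).** "To measure the cost-effectiveness of having CHWs manage malaria using Coartem® with RDTs compared to without the use of RDTs". Sections 4.18 and 6.2 describe the same contrast.
- **What the arms receive (4.2).** "The CHWs in the intervention arm will be supplied with RDTs, Coartem® and amoxicillin". Control CHWs have Coartem, do no RDT, and refer suspected pneumonia to a health facility.

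**The concern.** Three statements in the economic plan do not do what they are meant to do. The only test named for cost differences does not apply to costs summarised as means. The ratio uses a harmful outcome in a formula whose usual reading assumes a benefit, so a reader who takes it in the usual way reads it backwards. The ratio is also named for the RDT, although the arms differ in a second component that can change both cost and failure.

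At stake is the secondary hypothesis in section 3.3.2 that CHW use of Coartem is more cost-effective when RDTs guide it. Section 9.5 expects the results to inform national policy, so sign and attribution matter to readers who will not go back to the formula.

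**Working it through.** The protocol gives no cost, failure rate or CER value, so there is no stated figure to reproduce. Values marked as assumed are illustrations.

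**1. Chi-square on costs.** Input: 1320 febrile children (section 4.3, before drop-out inflation), taken as 660 per arm.

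Take the sentence literally: cross-tabulate arm by cost value, with every cost distinct.
- Each cost value is one column holding one child, so the expected count in each of its two cells is 0.5.
- Each cell contributes (0.5)²/0.5 = 0.5, and there are 2 × 1320 = 2640 cells, so the statistic is 2640 × 0.5 = 1320.
- Degrees of freedom are (2 - 1)(1320 - 1) = 1319, giving p = 0.487.

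The result does not depend on the costs. In simulated log-normal data it was the same for true mean ratios of 1, 2 and 5. A Welch t-test on the same data, simulated without clustering, gave p = 0.38, 1.8 × 10⁻¹⁶ and 4 × 10⁻³⁵.

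This is the extreme case. If costs were first grouped, the test would compare distributions over categories whose cut-points the protocol does not give, and it still would not estimate a difference in mean cost.

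**2. Clusters.** Section 4.3 says intracluster correlation has to be taken into account in the analysis as well as the sample size. The GEE in section 6.1 models log odds of inappropriate treatment, and section 6.2 does not extend it to costs. To show the scale if clusters were ignored, assume 33 children per cluster and an ICC between 0.05 and 0.25. These values come from the protocol's fever table; the ICC of costs is not given.
- Design effect = 1 + (33 - 1) × ICC, which is 2.6 at 0.05 and 9.0 at 0.25.
- True two-sided error of a nominal 5% test = 2[1 - Φ(1.96/√design effect)], which is 22% and 51%.

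**3. Sign of the ratio.** Assumed: cost difference of 2 units in either direction; failure 10% in the intervention arm and 15% in control.

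| Intervention result | As written, (CA - CB)/(OA - OB) | Per failure averted, (CA - CB)/(OB - OA) |
| --- | --- | --- |
| Costlier, fewer failures | 2/(-0.05) = -40 | 2/0.05 = +40 |
| Cheaper, fewer failures | -2/(-0.05) = +40 | -2/0.05 = -40 |

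In the usual reading, a positive ratio for a better intervention is a price paid per unit gained. As written, that case is negative, and the cost-saving case looks like a price.

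**4. Contrast.** Set section 3.3.1 beside section 4.2: the objective varies one component (RDT or none), while the arms vary two (RDT or none; CHW amoxicillin or referral). Both parts of the ratio can respond to the second.
- *Cost:* section 4.18 counts malaria and pneumonia care, including referrals.
- *Failure:* read literally, section 3.5 counts as a failure a control child with fever and fast breathing who is given Coartem, is referred, and receives an antibiotic at the facility. A comparable intervention child given amoxicillin by the CHW is not a failure on that ground.

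Illustration: assume a 5-point fall in failure and charge the full cost difference of 2 units to the RDT. If the RDT produced 100%, 50% or 25% of the fall, the cost per failure averted by the RDT is 2/0.05 = 40, 2/0.025 = 80 or 2/0.0125 = 160. Two arms cannot identify that share.

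**The case against.** **The chi-square sentence is one unadjusted step beside a valid model.** This stands in part. The regression includes study arm and is a legitimate kind of cost comparison. However, it states no cluster handling, and its outcome is malaria cost while the summary covers malaria and pneumonia. A reader might infer that the cost-effectiveness hypothesis itself would be decided by a chi-square test. The protocol does not support that: the hypothesis is addressed by the CER, which uses no such test. Nor does the text mention grouped costs, a rank test or a Wald statistic that would rescue the sentence.

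**Cluster handling can be left to an analysis plan.** Largely fair. Section 4.3 states the principle, and the protocol nowhere says clusters will be ignored for costs. The particular method is a matter of choice.

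**The sign is only a convention.** The magnitude is indeed unchanged. A reader might go further and say that the reversed sign makes a dominant result look like a dominated one. That ambiguity belongs to every single ratio. Per failure averted, cheaper with fewer failures gives -2/0.05 = -40, and costlier with more failures gives 2/(-0.05) = -40. Changing the sign does not remove it; showing the two differences does.

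**The bundle is deliberate.** This stands. The main objective is integrated management, section 3.3.2 states the failure hypothesis for the combination, and a package CER is valid. Only the RDT label is wrong.

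**Size of the mixing.** A reader might divide 524 by 2042 (524 + 1518) and conclude that about 26% of children carry the amoxicillin effect. The documents do not support this. These are sample-size targets for two hypotheses, and a child with fever and fast breathing may count toward both, so they are not a case mix.

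**Conclusion.** The concern holds in three limited parts.

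1. The chi-square test is inapplicable to mean costs. This is the clearest error. The planned regression mitigates it only partly, because its treatment of clusters is not stated.
2. The CER as defined has the opposite sign to the usual reading, with its magnitude unchanged. This follows directly from sections 4.18 and 6.3 read together.
3. The CER estimates the combined package, while sections 3.3.1, 4.18 and 6.2 name it for the RDT. The share due to the RDT cannot be determined from the design, so the size of any misattribution is unknown.

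The numerical costs, failure rates and RDT shares above are assumptions, and the error rates of 22% and 51% apply only if clusters were in fact ignored and costs had the ICCs assumed. The point concerns a secondary economic outcome. It does not touch the primary analyses, but it should be corrected before costs are analysed.

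**What to change.** 1. Replace the chi-square sentence with a comparison of mean costs between arms that accounts for clusters, reported with a 95% confidence interval. The planned regression on study arm with cluster-robust standard errors would do, as would an analysis of cluster-level means. State one cost scope (malaria, or malaria and pneumonia) for the summary and the regression.
2. Define the ratio as cost per failure averted, (CA - CB)/(OB - OA), with O the proportion failing treatment. Report the cost difference and the failure difference beside it.
3. In sections 3.3.1, 4.18 and 6.2, label the CER as that of the combined package of RDT-guided Coartem and CHW amoxicillin. An analysis in febrile children without fast breathing can be added as an optional supportive estimate for the RDT. It uses fewer children and leaves out the group with overlapping symptoms that motivates the study, so it answers a narrower question.

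The cost is a change of wording. CHWs in both arms already assess respiratory rate, and the cost and failure data are already planned, so no new collection is needed.

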###### Estimate of incremental cost per health outcome

Several of our specific secondary objectives will involve calculating cost-effectiveness ratios (CERs). Each CER will be estimated by calculating the difference in costs divided by the differences in health outcome according to the following standard cost-effectiveness formula:

*CER = (CA – CB) / OA – OB),*

Where C refers to total cost, O refers to outcome, A refers to the intervention group, and B refers to the control group.

###### Sensitivity analysis

We will conduct sensitivity analysis to determine which variables most significantly affect our results. This will be done by univariate and multivariate sensitivity analysis, as well as possibly Monte Carlo Simulation modeling, on our main economic outcome variables.

**7. Informed Consent Process**

As a community wide intervention, consent will be obtained at three levels. At the first level, community leaders and village headmen will be approached through the neighborhood health committees and briefed on the project and their consent and approval will be solicited. Community leaders will be given the opportunity to decide whether they want their communities to participate in the research. Communities whose leaders oppose the research will be excluded by not enrolling CHWs working in these communities. This process will be monitored by the local IRB.

The second level of consent seeking will be from the CHWs. This will be an informed consent. This is because in addition to collecting data on their performance, we also collect personal information including social and demographic data. The field coordinator with assistance from CHS and the Mazabuka and Siavonga DHMTs will visit all the CHWs supported by CHS in the study area. The project will be explained to them stressing their roles and responsibilities and the benefit to the community if the project proves feasible. It will be emphasized that there will not be any payment for their role in the project. It is only when they have signed an informed consent that they will be invited for training. Those who do not consent will not be trained and therefore patients they attend to will not be followed up.

The third level of consent will be from caregivers of children who will be followed up after receiving treatment from the CHWs. The consent is to allow us to collect data by which to assess the effectiveness of the intervention “CHWs delivery Coartem with the aid of RDTs and amoxicillin”, NOT for treatment per se as would be the case in a traditional efficacy trial.

The consent will be taken when the data collector makes the day 5-7 follow-up. It is only when the caregiver has signed or thumb-printed the consent form that the follow-up form will be administered. We will also take consent from respondents of the household surveys before they are interviewed.

The data collectors will take the consent for the follow-up visits and the household surveys. .In all cases the person obtaining the consent will explain the study, including all requirements and benefits to the community. All those consenting will be assured of the confidentiality of the data that will be collected. Those who are willing to participate will be asked to sign the written informed consent, which will be countersigned by the person obtaining the consent. Those who are illiterate will be allowed to thumbprint the consent form instead of providing a signature.

All consent forms will be developed in accordance with guidelines of Boston University’s IRB and the Ethics Committee of the University of Zambia. They will be translated into Tonga and then back-translated into English to ensure validity of their contents.

# 8.0 Data Safety Monitoring Board

We will constitute a data safety monitoring board to conduct an interim analysis at six months on the primary outcomes and review any serious adverse events that may occur in the study and make an independent determination of whether they are study-related or not. The DSMB members will be comprised of two Zambian scientists, possibly a statistician and a pediatrician and one US-based epidemiologist, none of whom will be directly involved in the study. The study will be stopped if during the interim analysis we find that the appropriate treatment for fast breathing is increased by 40% or more and inappropriate use of Coartem for fever is reduced by 40% or more in the intervention arm.

**9.0 POTENTIAL RISKS/DISCOMFORTS AND BENEFITS**

**9.1 Potential Risks/Discomforts to CHWs**

The CHWs' participation in the study may pose additional risk beyond what they would normally experience occupationally. The misuse or the perception of misuse of medication or misclassification could cause their reputation to be tainted or harmed in the community. This will be minimized through regular performance assessment and providing feedback to the CHWs. There is also the risk of pricking themselves during the performance of RDT. This will be minimized by emphasizing the need not to rush and to use extreme care when handling sharp objects and also how to dispose off sharp objects during the training. They will also be taught what to do in the event of them pricking themselves.

**9.3 Potential Risks/Discomforts to participants of the Household surveys.**

The interview may take time to complete and may cause some discomfort. The recall of illnesses and deaths may cause some upset and bring memories of grief and sorrow. The training of interviewers will be aimed at improving their communication and interviewing skills.

**9.4 Potential Benefits to study subjects**

The training the CHWs will receive will improve their skills and may increase their confidence in attending to children. The improved skills of the CHWs are likely to make them provide better quality of care, which will be beneficial to the patients they attend to including the participants of the study.

## 9.5 Potential Benefits to Society

## The results of this study may have an influence on national policy and thus lead to changes that would allow CHWs to use Coartem with RDTs and amoxicillin (efficacious drugs for malaria and pneumonia) at the community level. This will bring early and appropriate treatment of malaria and pneumonia (two of the leading cause of deaths in children) to many children in developing countries. This becomes particularly relevant to areas where this is little possibility of referral or the care taker cannot be referred (distance or other home obligations). This new approach might also result in decrease in the costs of care.

## 10.0 Study Organization and Implementation

## 10.1 Collaborators

## The study will be collaboration between the Center for International Health and Development of Boston University School of Public Health, The Ministry of Health of Zambia and the Chikankata Health Services of the Salvation Army Corp of Zambia. The Ministry of Health will be represented by the Child Health Unit, the National Malaria Control Center and the District Health Management Teams of Mazabuka and Siavonga Districts. The Chikankata Health Services and the DHMTs will be the implementation agencies while CIHD, the Child Health Unit of MOH and NMCC will provide the technical support and assistance. There will be a memorandum of understanding between these partners, which will be passed by the Ministry of Health Headquarters.

## 10.2 Study Coordination

There will be a study coordinator who will be responsible for overseeing implementation of field work and collection of the requisite data in collaboration with implementing partners. He will also be responsible for regular reporting to the BU research team and the Steering Committee, and for maintaining regular communication between the collaborating teams and community leaders. Requirements: ability to manage small field office, some data management skills, language skills, good interpersonal skills.

